#### Secondary outcome analysis

Mean differences at other time-points are obtained as additional post-hoc tests from the model used for the primary analysis. The analysis of secondary outcome variables will be performed analogously to the primary analysis. A sensitivity analysis will be performed, repeating the primary analysis using multiple imputation to deal with patients that have no outcome measures apart from baseline.

#### Prediction analysis

A prediction model will be ran on the intervention group (rehabilitation with optional delayed ACL reconstruction). Based on 5 variables we want to assess whether it is possible to predict whether the patients in the intervention group will need surgery or not (binary outcome). The event of ‘delayed surgery’ was considered as binary outcome and not as time-to-event since the main question is to investigate whether it is possible to predict who will need a delayed surgery. The timing of the delayed surgery is less relevant as the timing is often influenced by several personal factors such as work, school, holiday and also by the availability of the surgeon etc.

A logistic regression model will be used and a backward selection procedure will be applied for model selection. The performance of the model will be quantified by the area under the ROC curve (AUC). Internal validation will be performed by means of a leave-one-out cross validation method to obtain a more realistic estimate of the model performance.

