### Secondary objective

The secondary objective is to identify individuals who would benefit the most from reconstruction versus those who should rather be treated conservatively. A prediction model will be built in the intervention group (rehabilitation with optional delayed ACL reconstruction) to investigate this. Five predictor variables will be considered to predict whether delayed reconstruction is necessary. The following five variables will be considered:

KOOS QOL: patients with high scores on the KOOS QOL are less likely to require delayed ACL surgery [22].MRI features: patients with pathologic MRI features (fiber continuity disturbed, high/heterogenous signal intensity, more horizontal slope of ACL, unclear boundaries) are more likely to require delayed ACL surgery [16].hemarthrosis: patients with a lower degree of hemarthrosis detected by MRI are less likely to require delayed ACL surgery.IPQ-R (illness perception questionnaire): patients’ expectations play a crucial role in determining the success of non-surgical treatment [23].pre-activity level: patients who are less physically active prior to their injury are less likely to require delayed ACL surgery [24].

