### Sample size

The outcome(s) on which the sample size calculation is based upon is the KOOS QOL, a self-administered questionnaire. The outcome for the **non-inferiority analysis** is the change on the KOOS QOL between the baseline measurement and 1 year after randomization. The sample size was calculated using the power procedure in SAS 9.4 to show with 80% of power that conservative treatment is not inferior to standard treatment, where a non-inferiority margin of 7 (change-points) was adopted based on the study of Collins et al. who report a minimal detectable change in KOOS QOL of 7 points [33]. The analysis consists in estimating the difference in mean change-scores between both treatment arms with a one-sided 95% confidence interval (Corresponding to a 5% significance level). Non-inferiority will be concluded when the lower limit of the confidence interval will be above the non-inferiority margin of -7. An equal treatment effect in both arms and a standard deviation for the change-score of 19 were assumed for the sample size calculation [1]. Assuming a drop-out of 10%, a total number of 260 patients is required for randomization. For the **superiority analysis** the sample size was calculated to demonstrate with a two-sample t-test a difference between the two treatment groups with respect to the change in KOOS QOL score at 7 months follow-up compared to post-injury. Considering equal group sizes, a two-sided 5% significance level, 90% power, the smallest important difference as 13.5 change-points [31] a standard deviation of 18 for the change in KOOS QOL versus baseline [31], and a 10% drop-out rate, the calculation indicates a total sample size of 88 patients. Furthermore, the 5% significance level was adopted since a hierarchy of statistical testing will be used. Only if the non-inferiority test is significant at 12 months, the test of superiority at 7 months will be performed since superiority is judged necessary to change practice. Furthermore, a prediction model will be built in the intervention group (rehabilitation and optional delayed ACL reconstruction) with the event of delayed surgery as binary outcome and where an initial set of the five predictor variables described above will be considered. Following the rule of thumb of including at least 10 events per parameter in the model, this analysis requires at least 50 events (i.e. delayed surgeries in the experimental group). Assuming that 1/3 of patients in the experimental group will need delayed surgery (KANON Trial), a minimum of 150 patients will be needed in the intervention group in order to develop such a prediction model.

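### The leave-one-out AUC planned for the backward-selected prediction model is unstable and too low for weak-to-moderate models if selection is repeated in each fold, and omits selection optimism if it is not

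*Protocol article*

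**What the plan says.** The Protocol article, Secondary objective, sets the task: "Five predictor variables will be considered to predict whether delayed reconstruction is necessary". Under Prediction analysis the method is fixed: "A logistic regression model will be used and a backward selection procedure will be applied for model selection". The AUC is the only performance measure named there, and the validation step reads: "Internal validation will be performed by means of a leave-one-out cross validation method to obtain a more realistic estimate of the model performance".

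The size of the data set comes from Sample size: "Following the rule of thumb of including at least 10 events per parameter in the model", "this analysis requires at least 50 events". With one third of the conservative arm assumed to need delayed surgery, that gives a minimum of 150 patients in that arm.

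The article does not say how an AUC is formed from single held-out patients, whether backward selection is repeated in each fold, or which selection threshold applies. It sets no AUC value at which the model would count as useful or useless.

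**The concern.** An AUC compares events with non-events. A leave-one-out fold holds one patient, so it contains no such pair. The only AUC that leave-one-out can give is one that pools the predictions of about 150 separately fitted models and ranks them together.

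That ranking is distorted. Removing an event lowers the event rate in the training data, and removing a non-event raises it, so events are pushed slightly below non-events, against the true order. If selection is repeated, a fold that drops a predictor is also ranked against folds that keep it.

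The AUC is the sole stated measure for the secondary objective, and the conservative arm was enlarged to 150 to support this model. The Discussion says that no such evidence exists yet, so weak or moderate discrimination cannot be ruled out in advance. That is the range in which the planned statistic performs worst.

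**Working it through.** **Inputs from the Protocol article.** Five candidate predictors (Secondary objective); 10 events per parameter, an event rate of 1/3 and 150 patients (Sample size); logistic regression, backward selection, AUC and leave-one-out validation (Prediction analysis).

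**The plan's own figure.** 5 × 10 = 50 events; 50 / (1/3) = 150 patients. It reproduces.

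**Exact case: no predictor kept in any fold.** With 50 events and 100 non-events, each prediction is the event rate among the other 149 patients.

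- Held-out event: (50 − 1)/149 = 49/149 = 0.329.
- Held-out non-event: 50/149 = 0.336.

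All 50 × 100 = 5,000 event/non-event pairs are ranked the wrong way round, so the pooled AUC is 0/5,000 = 0. The true AUC of such a model is 0.5.

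**Simulation when predictors can be kept.** Assumptions, because the article gives none of these: five independent standard normal predictors, Wald backward selection at p<0.05 (also p<0.157), and the effect sizes in the table. Each setting had N = 150, about one third events and 400 data sets. True AUC means the AUC of the fitted model in 20,000 new patients. The bootstrap is optimism-corrected (40 resamples). The 5-fold AUC comes from repeated stratified 5-fold cross validation, averaged within test folds. Entries are means at p<0.05.

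| Coefficients | True AUC | Leave-one-out, reselection | Leave-one-out, no reselection | Bootstrap | 5-fold |
|---|---|---|---|---|---|
| all 0 | 0.500 | 0.116 | 0.138 | 0.484 | 0.500 |
| all 0.2 | 0.544 | 0.387 | 0.426 | 0.557 | 0.544 |
| all 0.3 | 0.595 | 0.530 | 0.581 | 0.615 | 0.586 |
| two of 0.5 | 0.647 | 0.599 | 0.626 | 0.647 | 0.637 |
| all 0.4 | 0.657 | 0.621 | 0.674 | 0.676 | 0.643 |
| one of 0.75 | 0.682 | 0.652 | 0.665 | 0.667 | 0.673 |
| all 0.55 | 0.737 | 0.722 | 0.750 | 0.748 | 0.722 |
| all 0.7 | 0.798 | 0.787 | 0.800 | 0.802 | 0.784 |

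- **With reselection**, the error runs from 0.530 − 0.595 = −0.065 for a weak model to 0.787 − 0.798 = −0.011 for a good one. At p<0.157 it is smaller: 0.511 against 0.568, 0.606 against 0.628, and 0.745 against 0.756.
- **Without reselection**, the error for true AUC of 0.595 and above runs from 0.626 − 0.647 = −0.021 to 0.674 − 0.657 = +0.017. The collapse remains when nothing is selected.
- **Bootstrap** is within 0.020 of the truth in every row.
- **No predictor kept:** 77% of data sets with no signal, 10% in the all-0.3 setting, 2% in the all-0.4 setting and none at all-0.55 or above. Where the full-data selection kept nothing, the leave-one-out AUC was exactly 0 in 96-100%.

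**Leave-one-out AUC at or below 0.5 although the fitted model discriminates.** When the true AUC was at least 0.65, this happened in 0-6% of data sets (bootstrap 0%). When it was at least 0.70, it happened in 0-1%, apart from 1 of 24 data sets in one setting.

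**Second simulation (120 data sets per setting, reselection, p<0.05).** Leave-one-out against true AUC: 0.122 against 0.500, 0.445 against 0.587, 0.587 against 0.639, and 0.695 against 0.703. At a true AUC of 0.64 the root mean squared error was 0.145, against 0.048 for the bootstrap. Among models with true AUC of at least 0.60, results at or below 0.5 occurred in about 0-13%, in settings with enough such models.

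**Third simulation (200 data sets per setting).** Restricted to fitted models with true AUC 0.60-0.70, results at or below 0.5 occurred in 2-17% at p<0.05 and 4-21% at p<0.157, depending on the setting. The bootstrap gave 0-2%.

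**The case against.** The strongest reply is that a model worth using is hardly affected. At a true AUC of 0.737 leave-one-out gives 0.722, the same as within-fold 5-fold, while the bootstrap errs by +0.011. This stands: from about 0.70 upwards the choice of method matters little.

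A reader might infer that the trial will report a useful model as no better than chance. The document does not support that. The AUC of 0 arises when selection keeps nothing, and then there is no useful model to misreport. A value of exactly 0 would also be recognised as an artefact. The article sets no AUC cut-off and no rule for declaring prediction impossible.

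A reader might also infer that the bias is always downward. That depends on reselection in each fold, which the article does not state and may leave to a fuller document. Without reselection the error can go either way. Neither option rescues the plan, however: with reselection the statistic is unstable and low for weaker models, and without it the selection step goes unvalidated.

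Finally, the article's claim of a more realistic estimate is fair as a contrast with the AUC in the development data, which is too optimistic. That stands too. The point is that better estimators than leave-one-out are available for this purpose.

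**Conclusion.** The point holds as a criticism of a stated method, not of a missing detail. Pooling over about 150 models follows from pairing leave-one-out with the AUC. At 150 patients and 50 events, with selection repeated in each fold at p<0.05:

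- about 0.59-0.62 is reported when the true AUC is about 0.64-0.66;
- about 0.45-0.53 is reported when it is about 0.59;
- 0 instead of 0.5 is reported when no predictor is kept;
- the shortfall is about 0.01-0.03 once the true AUC is about 0.70 or more.

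For moderate models the instability is the larger problem, with a root mean squared error about three times that of the bootstrap (0.145/0.048 = 3.0). Without reselection, the estimate omits selection optimism and can be slightly too high.

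The exact zero needs no assumption beyond 50 events in 150. The other sizes rest on assumed effect sizes, independent normal predictors and the selection threshold. Only the secondary prediction objective is affected.

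**What to change.** In Prediction analysis, replace leave-one-out cross validation with bootstrap internal validation (for example 500 resamples). Repeat the backward selection in every resample and report the optimism-corrected AUC as the model's performance. The alternative is repeated stratified 10-fold cross validation, with selection inside each fold and the AUC computed within each test fold and then averaged, never pooled over models. The simulations above used 5 folds for this alternative.

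The change is one sentence in the plan, a few lines of code and a little computing time. It needs no extra patients, visits or data, and leaves the primary analysis untouched.

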#### Explorative analysis

A similar method of analysis as described for the primary analysis (intention-to-treat) will be applied to the as-treated analyses.

### Data monitoring

#### Access to data

The investigator will permit trial-related monitoring, audits, ethics committee review, and regulatory inspection, providing direct access to all related source data/documents.

At the end of the trial, the funder (KCE) will have access to the study data. This will only be the pseudonymized study data.

### Safety recording and reporting

The risk of adverse events (AE) occurring due to the intervention in this trial is unlikely. Therefore, safety reporting will be limited to the safety reporting necessary for routine care. The participant will be asked to report any adverse event related to the study-specific intervention to the study team. The following adverse events will be registered at every follow-up visit: surgical complications, arthrofibrosis, infection, any additional acute injury to the ipsilateral or contralateral knee (such as re-injury, graft-rupture or contralateral ACL injury, lesions of menisci, cartilage or ligament,… ).

These reported events will be documented by the investigator in the source documents. In addition, the following minimum information should be recorded for each adverse reaction by the reporting investigator (AE description, start and stop date of the AE, severity, seriousness, causality assessment to the study interventions, and outcome). The sponsor will keep detailed records of all AEs reported to him by the investigators and will evaluate for seriousness, causality, and expectedness.

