## Background

Rupture of the anterior cruciate ligament (ACL) is a common injury, especially in young, physically active individuals, with an indicate rate of 0.7/1000 person-years in Belgium [3]. The ACL has an important role in both static and dynamic stabilisation of the knee joint with a primary role limiting anterior translation of the tibia relative to the femur. In more than 70% of the injuries, the rupture occurs during a non-contact mechanism, such as a sudden change of direction or landing with the knee near full extension [4]. Frequently, not only the ACL is ruptured but typically also injuries to the menisci, cartilage, collateral ligaments and subchondral bone are present. The rupture of the ACL and damage to other knee stabilising structures, often results in knee joint instability affecting daily activities and sports leading to poor knee related quality of life. Furthermore, ACL injuries are associated with increased risk of post traumatic knee osteoarthritis (PTOA) [5] and athletes who return to sport have a high risk to sustain a re-injury [6]. The medical community has always been convinced that surgical repair of the ACL was necessary to restore mechanical knee stability so that patients can safely return to sports [7], but also to avoid long term disadvantages such as persistent knee instability, re-injury [6] and PTOA [5, 8]. However, evidence assessing treatment outcomes after ACL reconstruction does not support these beliefs. Ardern et al. [9] found that only 55% of athletes who underwent an ACL reconstruction return to their preinjury sport level. Furthermore, a recent meta-analysis showed that about 50% of the patients who underwent surgical repair of their ACL have cartilage degeneration 20 years after surgery [10] and up to 23% suffer a new ACL injury (ipsilateral or contralateral) within two years after return to sport [11]. Based on these results, one can assume that ACL reconstruction offers no certainty of restoration of normal knee function and protection from long-term disadvantages. Besides, it is uncertain whether ACL reconstruction results in benefits at all compared to conservative treatment. In total, 3 RCTs compared the clinical effectiveness between ACL reconstruction and conservative treatment (= rehabilitation + optional delayed surgery): the KANON trial [1] COMPARE trial [2] and ACL SNNAP [12]). The KANON trial concluded that a strategy of early reconstruction plus rehabilitation did not provide better results at five years than a strategy of initial rehabilitation with optional delayed ACL reconstruction [1, 13].The COMPARE trial found slightly better self-reported outcomes (knee symptoms, self-reported knee function, and perception of the ability to participate in sports) in the immediate ACL reconstruction group compared with the conservative group at two years follow-up. However, none of these findings were considered clinically important. The SNAPP trial investigated chronic ACL ruptures and found that patients with chronic symptomatic ACL deficiency have better clinical outcomes if they undergo surgery [12].

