### Interventions

The study compares two standard treatment options for an acute ACL injury: [1] conservative treatment with optional delayed ACL reconstruction and [2] surgical treatment consisting of immediate ACL reconstruction and rehabilitation. We will not deviate from current practice, except for the randomization, to keep the trial pragmatic. Hence, the study does not predetermine the type of ACL reconstruction and patients will choose their own physiotherapist for the rehabilitation. However, to guarantee a minimum quality of rehabilitation, which is crucial for the integrity of the comparison, we will provide evidence-based guidelines and progression criteria for ACL rehabilitation to the physiotherapists.

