### Blinding

Given the nature of the trial, blinding of participants and care providers is not feasible.

Data collectors and data analysts will be blinded to the extent possible. Outcomes will be collected in the same way in both groups, e.g. by electronical questionnaires for which assessors and collectors can be blinded. However, because of the subjective and self-reported nature of the outcomes being assessed, detection bias may be a potential risk of bias. After all participants have completed the Trial, the database will be locked and the collected Trial data will be unblinded to allow analysis of the Trial data.

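### For adverse events off the fixed list, the only active route the safety section states is an unblinded participant's report of events related to an undefined intervention, so their capture may differ by arm

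*Protocol article*

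**What the plan says.** The section Safety recording and reporting opens with a premise, "The risk of adverse events (AE) occurring due to the intervention in this trial is unlikely", and draws a consequence from it: "Therefore, safety reporting will be limited to the safety reporting necessary for routine care". It then gives two ways in which events reach the study team.

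- **Participant report.** "The participant will be asked to report any adverse event related to the study-specific intervention to the study team".
- **Fixed list.** "The following adverse events will be registered at every follow-up visit: surgical complications, arthrofibrosis, infection", followed by any new acute injury to either knee, "such as re-injury, graft-rupture or contralateral ACL injury" among the examples. No relatedness condition applies to the list.

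The investigator then records a minimum data set that includes a causality assessment, and the sponsor evaluates seriousness, causality and expectedness.

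Three other places bear on this. The Adverse events entry under Secondary outcomes names the same events but introduces them as examples, with no relatedness condition. Interventions says of the two arms: "We will not deviate from current practice, except for the randomization, to keep the trial pragmatic". Blinding says that "blinding of participants and care providers is not feasible".

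**The concern.** Adverse events are a stated outcome of a trial that compares surgery with rehabilitation, so harms should be collected in the same way in both arms. For off-list events, the safety section puts a causality judgement first and gives it to the person least able to make it neutrally, a patient who knows the treatment received. An operated patient may readily connect a later medical event with the operation. A patient in rehabilitation may see no connection between the same event and exercise. The later causality steps cannot correct this, because the investigator and sponsor assess only what reaches them.

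The premise used to limit reporting is also awkward. The section calls intervention-caused events unlikely, yet a few lines later lists harms that follow from surgery, and surgery is one of the two randomised strategies.

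**Working it through.** The plan states no figure to reproduce. The check is a comparison of the protocol article's own sections, with one small count for context.

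1. **What the relatedness phrase refers to.** Interventions describes both arms as standard options, with randomisation as the only departure from practice. Read strictly, nothing is then specific to the study. Elsewhere (Secondary objective, Sample size, Prediction analysis) the term intervention group means the conservative arm alone, and Primary outcome analysis sets it against a control group. Later in the safety section, causality is to be assessed against the study interventions in the plural. The phrase could therefore cover no treatment, one arm or both.

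2. **Who applies it.** The participant does, and participants are not blinded. The Blinding section itself names detection bias as a risk for self-reported outcomes.

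3. **Order of the steps.** Off-list event → participant judges relatedness → report → investigator and sponsor assess causality. An event screened out at the second step never reaches the fourth.

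4. **Whether the list closes the gap.** For knee injuries and infection it does, in both arms. For other events it does so only in part, because surgical complications can by definition arise only in someone who has been operated on. Take an admission that is neither an infection nor a knee injury. After surgery it can be registered as a surgical complication, with no filter. In an unoperated patient it is off the list and depends on the patient attributing it to treatment.

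5. **How operated patients divide between the arms.** Randomization allocates 130 to immediate reconstruction and 150 to conservative treatment. Sample size assumes that one third of the conservative arm will have delayed surgery; Background reports 50% at two years in one earlier trial.
   - Operated in the conservative arm: 150 × 1/3 = 50, or 150 × 0.50 = 75.
   - Not operated: 150 − 50 = 100 (67%), or 150 − 75 = 75 (50%).

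   So the surgical category is not exclusive to one arm, but half to two thirds of the conservative arm would never fall under it, against few or none in the other arm if allocation is followed. This shows where capture can diverge. It does not give the amount of bias, since the documents contain neither a rate of off-list events nor a reporting probability.

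6. **Outcomes section against safety section.** The first is open-ended and unconditional. The second has a closed list plus related events. A site following one would collect differently from a site following the other.

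7. **The low-risk premise.** Besides the listed surgical harms, the Discussion describes surgery as adding iatrogenic trauma that unoperated patients are spared. Neither fits easily with calling intervention-caused events unlikely.

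**The case against.** The strongest reply is that the participant sentence adds a route and is not a gate. The outcomes section is open-ended, Table 2 schedules adverse events at V3 to V7 for everyone, and routine-care safety reporting continues. This stands to the extent that one cannot say off-list events are collected only when the patient thinks them related. It remains true that the safety section states no other active route for them, and that the outcomes section does not match it.

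A second reply is that targeted collection is a defensible choice in a pragmatic trial of two standard treatments, and that the full protocol may say more. That is fair, and nothing here rests on missing detail. The point concerns a rule the article does state. Targeting by event type would be unobjectionable; targeting by the patient's view of cause is the difficulty.

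A third is that the adverse event named in the abstract, re-rupture, is on the list. This stands in full: comparisons of re-injury, graft rupture and contralateral ACL injury are untouched.

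A reader might go further and set the premise against the Background, where "up to 23% suffer a new ACL injury (ipsilateral or contralateral) within two years after return to sport" is reported for reconstructed patients. The documents do not support that use. The figure is an upper bound, covers either knee, is counted after return to sport, is not attributed to the operation and has no conservative comparator. It therefore cannot contradict a statement about intervention-caused events. Nor does it show a collection gap, because those injuries are registered at every visit without any relatedness condition.

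**Conclusion.** The point holds in a narrow form. The safety section's wording lets capture of off-list adverse events depend on an unblinded participant's attribution to an undefined intervention, and the surgical category on the list leaves unoperated patients more exposed to that filter. Capture may therefore differ by arm.

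The size is unknown. If patients in both arms report off-list events equally, there is no bias. A difference arises only if sites apply the participant sentence as written, attribution differs between operated and unoperated patients, and off-list events are compared between the arms. None of this can be quantified from the documents, and a reader should not infer that a biased harms comparison has been shown. The KOOS QOL analyses and the listed events are unaffected.

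The sentence calling intervention-related events unlikely is inconsistent with the surgical harms the article itself names. This is a worthwhile, low-cost improvement and not a threat to the trial's main conclusions.

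**What to change.** In Safety recording and reporting:

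- Delete the condition that the participant must judge the event related.
- At the existing visits V3 to V7, ask one identically worded question in both arms about the listed events and about any serious event (hospital admission or unplanned operation), regardless of presumed cause.
- Leave causality to the investigator and sponsor steps already described there.
- Delete or reword the sentence calling intervention-related events unlikely. It cannot be replaced by expected rates, since the article gives none for surgical complications, arthrofibrosis or infection.

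Align the Adverse events entry under Secondary outcomes with the revised text, so that both sections define the same set of events.

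The cost is a wording change and one standard question at visits that already take place. The downside is that some serious events unrelated to treatment will also be recorded and assessed.
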